## 2.8 Subject privacy and confidentiality

The Sponsor-PI affirms and upholds the principle of the subjects right to privacy and that they shall comply with applicable privacy laws. Especially, anonymity of the subjects will be guaranteed when presenting the data at scientific meetings or publishing them in scientific journals.

Individual subject medical information obtained as a result of this study is considered confidential and disclosure to third parties is prohibited. Subject confidentiality will be further ensured by utilising subject identification code numbers to correspond to treatment data in the computer files. All information (i.e., Name, Address, Date of birth etc.) that could identify the subject will be replaced by a code. People who do not have access to this key list cannot connect the information with the subject. The code list will never leave the University Hospital Basel. It will be protected with adequate encryption and will only be accessible to authorized persons. For data verification purposes, authorised representatives of the Sponsor-Investigators (e.g. monitoring institution) or an EC may require direct access to parts of the medical records relevant to the study, including subjects’ medical history.

*See Appendix C- US Protocol Amendments

## 2.9 Early termination of the Investigation

The Sponsor-Investigator may terminate the investigation prematurely according to certain circumstances, for example:

- ethical concerns,
- insufficient patient recruitment,
- when the safety of the patients is doubtful or at risk, respectively,
- alterations in accepted clinical practice that make the continuation of a clinical investigation unwise or
- early evidence of benefit or harm of the experimental intervention

**Stopping rules as defined by DSMC**

The DSMC will stop the investigation if the procedure shows harm according to the procedure laid down in the DSMC charter. Interim analysis regarding safety endpoints (SAEs and mortality) will be done after 63 (25%), 126 (50%), and 189 (75%) subjects were enrolled as defined in the DSMC charter.

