# 9. CLINICAL INVESTIGATION ASSESSMENTS

## 9.1 Clinical investigation flow chart/ table of clinical investigation procedures and assessments

[figure not shown]

The Schedule of assessments to be performed at each study visit is listed in the table below

| **Schedule of assessments** | | | |
| --- | --- | --- | --- |
| **Visits** | | **0** | **1** |
|  |  | **Screening and enrollment** | **Intervention** |
| **Assessment** | **Time Window** | 0 | 0 – 4 hours after Non-contrast MDCT scan |
|  | **Method** | Clinical Visit | Intervention |
| Informed consent | | X^1^ |  |
| Patient demographics (i.e. age, gender, pre-existing conditions) | | X |  |
| National Institute of Health Stroke Scale | | X |  |
| Pregnancy test (only in women of childbearing potential) | | X |  |
| Patient logistics (i.e. time from onset to admission / imaging) | | X |  |
| Medical history (including medication) | | X |  |
| Non-contrast MDCT head scan^2^ | | X |  |
| Enrollment | | X |  |
| Non-contrast syngo DynaCT Sine Spin FDCT head scan | |  | X |
| AEs | | Only if procedure related up to 24 hours after procedure | |
| SAEs | | Only if procedure related up to 24 hours after procedure | |

1. Post-hoc consent if patient was not able to give consent at trial inclusion (according to national and applicable law)

2. For clarification the MDCT scan could have been done in an external hospital (in case of transfer patients) if the images of the MDCT are available at the PACS of the enrolling hospital and the quality was deemed to be sufficient by the enrolling physician and all other in- and exclusion criteria are met

AEs Adverse events, FDCT Flat-detector CT, MDCT Multi-detector CT, SAEs Serious adverse events

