### 9.2.4 Assessment of safety outcomes

All AEs up to 24 hours after the procedure are investigated and documented in the source document. They are collected in the appropriate eCRF if they are deemed to be related to the procedure.

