#### 9.2.4.1 Adverse events

All AEs, which are deemed to be procedure related by the local PI and occur during the conduct of the clinical investigation and/or within 24 hours of the intervention or till discharge (whatever happens earlier) of the subject are collected and documented on an ongoing basis. Due to the nature of the intervention, there are no foreseeable AEs

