# 10. SAFETY

According to Swiss legislation there is no general obligation for the systematic documentation of adverse events (AEs) in medical device category A clinical investigations.^51^

**Adverse Events (AEs)** deemed to be related to the procedure under investigation (Adverse Device Effect) and all **Device deficiencies (DD)** are collected, fully investigated and documented in the source documents and appropriate case report forms (CRF) during the entire investigation period, i.e., from patient’s enrolment until the last CIP specific procedure, including a safety follow-up period of 24 hours. Serious adverse events which lead to death of the patient within 24 hours of enrolment will also be collected, fully investigated, and documented in the source documents and appropriate case report forms (CRF) independently of their causality.

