## 10.2 Adverse events categorization

The adverse events are categorized by the PI and the Sponsor using the following algorithm:

Does the AE meet the seriousness criteria?

- - No, it is not serious
    - - Is the relationship to the device or the procedure possible, probable or causal?
      - No: non-related AE
      - Yes: ADE
  - Yes, it is serious: SAE
    - - Is the relationship to the device or the procedure possible, probable or causal?
      - No: non-related SAE
      - Yes: SADE
  - Is it anticipated (within expected type, severity and frequency of the complications)?
    - - No: unanticipated SADE (USADE)
      - Yes: anticipated SADE (ASADE)

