### 10.3.2 Reporting of Safety related events Reporting to the Sponsor

All SAEs, device deficiencies and health hazards that require measures are reported to the Sponsor by the PI (or authorized designee) within 24 hours after becoming aware of the event. Device deficiencies are assessed regarding their potential to lead to an SAE.

Reporting to the Competent Ethics Committee:

The following events are to be reported to the CEC promptly (Art. 33 ClinO-MD):

1. any serious adverse event which has a causal relation with the MD (rating at least possible), comparator or procedure/test method or where a causal relation appears to be possible (SADE);
2. any device deficiency which, in the absence of appropriate measures or intervention or in less favourable circumstances, could have led to serious adverse events (DD with SADE potential);
3. any new information relating to an event already notified under points (1) and (2).

In order to ensure prompt notification, the Sponsor may initially submit an incomplete notification. If safety and health hazards that require measures must be taken immediately during the conduct of the investigation, the Sponsor notifies the CEC within 2 days of these measures and the circumstances which made them necessary (Art. 34 ClinO-MD).

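### Sections 2.9, 9 and 10 give conflicting rules on which SAEs and deaths are recorded for the DSMC and until when, so the non-fatal SAE listing depends on which section a site follows

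*Protocol*

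**What the plan says.** Section 2.9 makes the DSMC responsible for harm: "The DSMC will stop the investigation if the procedure shows harm according to the procedure laid down in the DSMC charter". The data it looks at are named next: "Interim analysis regarding safety endpoints (SAEs and mortality) will be done after 63 (25%), 126 (50%), and 189 (75%) subjects were enrolled". SAEs is not qualified there as all or related only. Section 1.7 gives the same three meeting points.

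The capture rules are spread over several places:

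- The Investigation Schedule and its copy in section 9.1 carry the same entry for AEs and for SAEs: "Only if procedure related up to 24 hours after procedure".
- Section 9.2.4 starts broadly ("All AEs up to 24 hours after the procedure are investigated and documented in the source document") but then limits eCRF entry to events considered related to the procedure.
- Section 9.2.4.1 gives the relatedness call to the local PI and ends collection "within 24 hours of the intervention or till discharge (whatever happens earlier) of the subject".
- Sections 10 and 10.3 collect related AEs from enrolment to 24 h after the last study procedure, then add: "Serious adverse events which lead to death of the patient within 24 hours of enrolment will also be collected". These fatal events are entered whatever their cause.
- Section 10.3.2 has no relatedness filter: "All SAEs, device deficiencies and health hazards that require measures are reported to the Sponsor by the PI (or authorized designee) within 24 hours" of awareness.
- Section 10.2 assigns causality to two parties ("The adverse events are categorized by the PI and the Sponsor using the following algorithm"), and its outcomes include non-related AEs and non-related SAEs.

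Section 10.3 also names the eCRF as the route for AE, device deficiency and SAE information, and says that no related SAEs are expected.

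**The concern.** The study has no control group (section 7.3), so the DSMC's signal is the number and pattern of serious events and deaths. For a non-fatal SAE that the local PI judges unrelated, the schedules and 9.2.4 keep it out of the eCRF, 10.3.2 requires it to be reported, and 10.2 requires the sponsor to form its own view of it. Sites cannot meet all of these as written. With up to 30 sites, the listing at each review would partly reflect which section each site follows.

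What is at stake is whether the DSMC can interpret what it receives. A short or blank list of non-fatal SAEs could mean that few occurred, or that sites filtered them out before entry. An unattributed worsening around the scan or the transfer to the angiography suite is the kind of pattern an independent committee is there to notice. Under the schedule rule it is seen only if the site has already linked it to the procedure. The primary accuracy analysis is not affected.

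**Working it through.** **Review points.** Total 252 (section 6.1). 0.25 × 252 = 63, 0.50 × 252 = 126, 0.75 × 252 = 189. The figures in 2.9 reproduce exactly, and the last planned review is at 189 patients.

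**Which events reach the eCRF or the sponsor.**

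| Event | Schedules, 9.2.4, 9.2.4.1 | 10, 10.3 | 10.3.2 |
|---|---|---|---|
| Related SAE | yes | yes | yes |
| Death, unrelated, within 24 h of enrolment | no | yes | yes |
| Death, unrelated, later than 24 h from enrolment but within 24 h of the scan | no | no | yes |
| Non-fatal SAE, unrelated | no | no | yes |

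The last three rows conflict. Section 10.2 fits only the last column, since a non-related SAE can be classified by the sponsor only if the sponsor receives it.

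**End of collection.** Let t be the time from enrolment to the FDCT.

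- AE window (schedules, 4.4, 5.2, 10): closes at t + 24 h from enrolment.
- Section 9.2.4.1: the earlier of t + 24 h and discharge.
- Any-cause deaths (10, 10.3): 24 h from enrolment.

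The first and third differ by t. Section 6.1 allows up to 4 h from enrolment to the last assessment, so the AE window closes at 28 h at the latest and the gap is at most 4 h. It will usually be much shorter. Section 9.3.2 counts its 4 h limit from the MDCT, enrolment comes after the MDCT, and 6.1 expects under 30 minutes between scans for most directly admitted patients.

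**Non-fatal SAE listing.** The protocol gives no event rate, so I assume p = 5% to 15% of patients with a non-fatal SAE within about 24 h, none judged related (section 10.3's own expectation). Expected count = n × p if all are reported, and about 0 if only related events are entered.

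| n | Related only | All SAEs (5% to 15%) |
|---|---|---|
| 63 | about 0 | 3.2 to 9.5 |
| 126 | about 0 | 6.3 to 18.9 |
| 189 | about 0 | 9.5 to 28.4 |

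If sites enrolling a fraction f of patients follow 10.3.2, the expected count is f × n × p. The DSMC cannot separate f from p.

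**Mortality listing.** Under section 10 any-cause deaths within 24 h of enrolment are entered. The chance that a review sees none is (1 − p)^n, with p the assumed 24 h death rate:

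| p | n = 63 | n = 126 | n = 189 |
|---|---|---|---|
| 0.5% | 73% | 53% | 39% |
| 1% | 53% | 28% | 15% |
| 2% | 28% | 8% | 2% |
| 5% | 4% | 0.2% | <0.1% |

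A review with no deaths is possible at low rates, but by chance and not because of the collection rule.

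**The case against.** The best defence is that the protocol, read as a whole, already captures more than the schedules suggest. Deaths within 24 h of enrolment go into the CRF regardless of cause, all SAEs go to the sponsor, and all AEs are documented in source. The bar for relatedness is low: under 10.1 and 10.3 a weak link that cannot be ruled out is enough, so many events close to the scan would pass it. Sections 10 and 10.3 note that Swiss law imposes no general duty to document AEs systematically in a category A investigation, and filtering by relatedness can be a proportionate choice for one 7-second scan without contrast. With no control group and no stated background rate, a full SAE list would also be hard to judge. Finally, the DSMC charter is a separate document and may define the listing.

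Most of this stands, and it limits the finding. A reader might infer that the safety reviews could be empty altogether, or that about 0 SAEs and deaths out of 252 would come before the DSMC. The documents do not support either. The expectation of no events in 10.3 concerns related SAEs only, deaths have their own cause-free route, and the last review is at 189.

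The defence does not remove the conflict over unrelated non-fatal SAEs. Source records stay at the site, 10.3.2 contradicts the 9.2.4 eCRF rule without saying which prevails, and a charter cannot list data that sites were told not to enter. If filtering is the deliberate choice, 10.2 and 10.3.2 are worded wrongly.

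**Conclusion.** The point holds as an internal conflict in safety data capture. The protocol gives incompatible rules for unrelated SAEs, three different ends of collection, and an unqualified term in 2.9 for what the DSMC reviews. In consequence the non-fatal SAE listing is either near zero or dependent on site practice: about 0 against about 9 to 28 events by the 189-patient review at assumed rates of 5-15%. The mortality listing is not empty by design. Its defects are that the schedules and 9.2.4 omit the any-cause rule, and that its window can close before the AE window by at most 4 h, usually much less. The discharge cut-off in 9.2.4.1 adds a further difference for patients who leave within 24 h.

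The conflict itself rests on the text alone. The event counts rest on assumed rates, and what the DSMC actually receives depends on a charter that is not available here. This should be corrected, but it does not bear on the primary endpoint.

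**What to change.** Use one capture rule and one window in the Investigation Schedule, 9.1, 9.2.4, 9.2.4.1, 10, 10.3 and 10.3.2. State in 2.9, in line with the DSMC charter, whether SAEs means all or only related ones.

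The rule that fits 10.2 and 10.3.2 as they stand is to enter every SAE and every death in the eCRF regardless of causality, from enrolment to 24 h after the FDCT, with no discharge cut-off. The relatedness filter would stay for non-serious AEs. The PI and the sponsor then each rate causality, and the DSMC receives that listing. The text should also say when collection ends for a patient who is enrolled but not scanned, for example 24 h after enrolment. If the sponsor intends related SAEs only, then 2.9, 10.2 and 10.3.2 need rewording to say so.

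The cost is a wording amendment and an eCRF check. Sites already document all AEs to 24 h in source, so the added work is entering the serious ones. The downside is more unrelated stroke SAEs to enter and review, and a status check for patients discharged before 24 h.

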**Stopping rules for the individual patient**

A trial patient or his/her next of kin/LAR can withdraw the consent to participate in the investigation at any time and without any declaration of reason. In this case the data collected until the time of withdrawal will be included for evaluation in order to not compromise the validity of the clinical trial or its results.^1^ This also applies if the patient dies before it has been possible to obtain consent or refusal or in the absence of a statement of wishes, but only if the consent of a next of kin/LAR has been obtained.^1^ These data will be kept coded. If a patient was included into the trial without prior consent from the patient and the patient or his/her next of kin/LAR refuses to give post-hoc consent all data from this patient must be erased. This patient will be replaced by another patient.

## 2.10 Clinical investigation plan amendments

Substantial amendments are only implemented after approval by the CEC (Art. 15 ClinO-MD). Amendments can only be submitted by the Sponsor-Investigator. For USA, substantial amendments will be provided after approval by the Swiss lead EC to the US chair who is responsible to obtain the approval by their local responsible EC.

All non-substantial amendments are communicated to the CEC together with the Annual Safety Report

(ASR) (Art. 15 ClinO-MD). The ASR shall include any deviations from the CIP that may have affected the rights, safety or well-being of the subject or the scientific integrity of the investigation (ISO14155).

*See Appendix C- US Protocol Amendments

## 2.11 Deviation from the Clinical Investigation Plan

The use of waivers from the CIP is prohibited (Annex XV, Chapter 2, Art. 3.10 MDR).

Under emergency circumstances, deviations from the CIP to protect the rights, safety and well-being of human subjects may proceed without prior approval of the Sponsor-Investigators and the EC. Such deviations shall be documented and reported to the Sponsor-Investigator and the EC as soon as possible. Otherwise, deviations from the CIP are not permitted.

All CIP deviations will be analysed by the Sponsor-Investigator and the US Chair of the Investigation and addressed with the local PI responsible for the CIP deviation. The Sponsor-Investigator will work together with the local PI on solutions to prevent CIP deviations in the future and also record in writing the results of these consultations. In case of repetitive CIP deviations an investigator can be disqualified from the investigation.

*See Appendix C- US Protocol Amendments

## 2.12 Pregnancy

Evidence of an ongoing pregnancy prior to randomization is an exclusion criterion. A negative pregnancy test must be obtained for all persons of childbearing potential prior to randomization. However, if a pregnancy emerges after the intervention, this will not result in the exclusion of the patient.

As the MDCT is **not** part of the clinical investigation it is at the discretion of the treating physician to perform the pregnancy test prior to the MDCT. However, if it is decided that the patient is a candidate for the trial a pregnancy test must be performed. Due to the possible time delay of up to four hours between the MDCT and the FDCT this is feasible.

# 3. BACKGROUND AND RATIONALE

## 3.1 Background and Rationale for the clinical investigation

Despite concerted efforts, stroke is still one of the leading causes of mortality and disability worldwide.^26-28^ Stroke can be divided into two main types: ischemic and hemorrhagic stroke. In severely affected patients, which will most likely be disabled or dead after the stroke - if not timely treated - roughly 80% of the strokes are caused by a vessel occlusion (i.e., ischemic strokes) and 20% are due to an intracranial bleeding (i.e., hemorrhagic stroke).

For acute ischemic stroke (AIS) patients due to a vessel occlusion, mechanical thrombectomy (MT) has substantially reduced the burden of disease. However, still roughly 50% of all AIS patients due to a large vessel occlusion (LVO are severely disabled after the stroke or die within 90 days after the stroke.^7, 8^ Since all neuroprotective trials so far have failed to show any beneficial effect in such patients^33, 34^, patient triage is an important area of inquiry due to the high time-dependency of the efficacy of MT.^9^ On average one minute delay in time to treatment causes the irreversible loss of 1.9 million neurons, 14 billion synapses and 12 km of myelinated fibers.^35^ Especially the door to puncture time is an independent variable for patient outcome as was shown in an analysis of 6,756 AIS patients with an LVO. Among every 1,000 patients treated, every 15-minute decrease in door-to-puncture time was associated with 21 (95%-CI 8 – 34) more patients discharged to home, 18 (95%-CI 4 – 31) more patients having freedom from disability and 22 (95%-CI 7 – 37) more patients having functional independence at discharge. It was further associated with 15 (95%-CI 4 – 26) fewer in-hospital deaths or patients being discharged to a hospice.^24^ These results were further validated by other study groups.^9, 22, 23^ Reducing time-delays in AIS patients has also important implications on a socioeconomic level as was recently shown by Kunz et al. They concluded based on the data of 7 large randomized controlled trials (RCTs) that every 10 minutes of earlier treatment result in an average gain of 39 days (95% prediction interval 23 – 53) of disability free life, translating to a reduction of $10,915 (95% prediction interval $5,928 - $15,365) of life-time healthcare costs.^29^

As there are still no reliable pre-hospital tests for the detection of an LVO or for the differentiation of ischemic or hemorrhagic stroke, the optimization of intra-hospital pathways is as of today one of the most promising research topics in stroke treatment.^16, 36^ As of now, the optimized conventional workflow consists of a rapid clinical assessment of the patient, followed by diagnostic imaging with multi-detector CT and CT angiography (MDCT and MDCTA) in the CT room and MT of eligible patients in the angiography suite. This workflow leads in highly trained centers to a door-to-groin time of approx. 60-70 min.^37^ Logistical circumstances such as patient positioning and transport to separate rooms hinder further time reductions.

A potential solution to this problem is to do both imaging and subsequent MT in the angiography suite using non-contrast syngo DynaCT Sine Spin (FDCT) for the exclusion of intracranial hemorrhage and flat detector CT angiography (FDCTA) or digital subtraction angiography for diagnosis of LVO. This would omit the need for another stop in the MDCT room and allow for direct transfer of the patient to the treatment room.^10^ We and other workgroups were already able to show in large patient cohorts that this optimized “direct to angiography” workflow can reduce door to groin times to under 30 minutes.^11-13^ These results were confirmed by our recent meta-analysis.^38^

However, the widespread implementation of this direct to angiography workflow has been impended by the difficulty of differentiating between ischemic and hemorrhagic stroke with FDCT.^39, 40^ As it is not possible to differentiate between ischemic and hemorrhagic stroke without brain imaging, it is of pivotal importance that hemorrhage exclusion can be performed safely and reliably with native FDCT imaging as well. A missed intracranial hemorrhage, i.e. an hemorrhagic stroke (which make up between 15 and 20% of all severely affected stroke patients according to an analysis of the Swiss Stroke Registry) could have potentially dramatical (and lethal) consequences due to different treatment strategies.^41^ Up till now this was only evaluated in retrospective studies, which showed very high sensitivity and specificity in the detection of intracranial hemorrhage with the last generation of FDCT.^6, 18^ However, prospective high-quality studies with large patient cohorts on this topic are still missing. We further did not find any ongoing studies on clinicaltrials.gov or within the WHO trial registry.

Therefore, we aim with this study to investigate if non-contrast syngo DynaCT Sine Spin imaging is non-inferior to non-contrast MDCT imaging regarding its sensitivity and specificity for the detection of intracranial hemorrhages. Non-contrast syngo DynaCT Sine Spin imaging will be deemed non-inferior if the lower bound of the 95%-confidence interval (95%-CI) of the sensitivity is above 95% and the lower bound of the 95%-CI of the specificity is above 95% (pre-defined non-inferiority margin). If non-inferiority could be established, this would guarantee for a safe triage of stroke patients. We are confident, that if our study shows non-inferiority of non-contrast syngo DynaCT Sine Spin imaging it will pave the way for the widespread implementation of the above described direct to angiography workflow, allowing more AIS patients to live a self-sustained, independent life after their stroke. Due to the high burden of disease any measurement of improvement is of high need. Conversely if our study fails to establish non-inferiority of non-contrast syngo DynaCT Sine Spin imaging for the detection of intracranial hemorrhage, it might prevent patients from undergoing harmful treatments.

